##### Patient file reviews

During the baseline data collection period and throughout the implementation phase, fieldworkers will capture the outcome of the psychological distress questionnaire found in the MCRs of pregnant women attending healthcare facilities. The information obtained will be used to assess whether delivering the HSS interventions improved (i) detection and referral rates, (ii) uptake of the detection and referral interventions, and (iii) the sustainability of the detection and referral interventions.

##### Documentation reviews

Reviewing registers and referral forms will be used to assess the coverage of the detection, referral, and treatment interventions. Rates of detection and referral for women with CMDs and experiences of domestic violence will be assessed before the intervention, and monitored weekly throughout the intervention period, by triangulating information obtained from (i) a review of the daily patient registers completed by ANC nurses and (ii) reviewing the referral forms completed by ANC nurses for patients who screen positive and agree to counselling.

The proportion of perinatal women with CMDs and experiences of domestic violence who take up the referral and receive partial or full treatment will be assessed by triangulating information obtained from reviewing the referral and counselling feedback forms to be completed by OTLs for all patients who are referred for the task-sharing psychological counselling programme.

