##### Addressing low levels of detection

Training, delivery of individual-level care, and audit and feedback were selected as the HSS interventions to address the low levels of detection. ANC nurses will be trained to screen all pregnant women for symptoms of CMDs and experiences of domestic violence as part of routine care, using the mental health screening questionnaire [12] available in the MCR [11] and the PACK guidelines [26]. The training material was developed in conjunction with the Knowledge Translation Unit (KTU), a clinical research unit at the University of Cape Town, that led the development of PACK. The PACK guide was used as the foundation for the detection and referral process. A *PACK Antenatal Women and Mental Health Module* [27] was developed to strengthen the mental health component of routinely provided antenatal care. Four case studies formed the backbone of the module, complemented by HSS discussions, completion of relevant stationery, and a focus on effective communication strategies. PACK facility trainers were the recipients of the master training and will be tasked with training ANC nurses at their facilities. The cascaded training will consist of four, weekly, 2-hr training sessions.

During the implementation phase, audit and feedback will be used to assess the screening rates at facilities and provide feedback to the relevant ANC nurses and their managers at bi-monthly meetings.

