##### Addressing poor linkage to care

Referral systems, training and audit, and feedback were selected as the HSS interventions to address the poor linkage to care. Standardised referral pathways were developed. PACK facility trainers (facility-based healthcare workers who are PACK trained and assigned to deliver PACK training to healthcare workers in their own facility) were the recipients of the master training and will be tasked with training ANC nurses at their facilities. ANC nurses will be trained to assess the severity of symptoms in pregnant women who screen positive and to use the standardised referral pathways to link them to care. Pregnant women with mild to moderate symptoms of depression will be referred to CHWs, while women with severe symptoms of depression will be referred to healthcare workers providing specialised care such as medical officers, psychiatric nurses, and psychologists. Pregnant women experiencing domestic violence will be referred to a social worker for support.

During the implementation phase, audit and feedback will be used to assess the referral rates at facilities and provide feedback to the relevant ANC nurses and their managers at bi-monthly meetings.

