Observation of health promotion talks	Assess uptake, fidelity, penetration, and sustainability of health promotion talks	Checklist to be completed by fieldworkers observing the talks		During the delivery of health promotion talks
Cohort study	Assess the presence of and risk factors for CMDs and experiences of domestic violence; assess whether the HSS interventions to improve awareness, detection, referral, and treatment resulted in improvement in clinical outcomes	Interviewer-administered questionnaires: Edinburgh postnatal depression scale [34]; psychological distress screening tool [12]; bespoke questionnaire to assess domestic violence; Household Food Insecurity and Access Scale [35]; Composite Abuse Scale [36]; WHO Disability Assessment Schedule [37]; Multidimensional Scale of Perceived Social Support [38]; Mother-to-Infant Bonding Scale [39]	Pregnant and postnatal women attending antenatal care clinics	Three timepoints — (1) when pregnant women are recruited, (2) when participants are 36 weeks pregnant, and (3) 6 weeks after participants have given birth
Patient file reviews	Assess changes in detection and referral rates of pregnant women with CMDs and experiences of domestic violence	Maternity case record [11]	Pregnant and postnatal women attending MOUs and BANC clinics	Weekly during the implementation phase
Documentation review	Assess coverage of the detection, referral, and treatment interventions	Bespoke patient registers and tracking forms	ANC nurses and OTLs	Daily during the intervention period
Counselling competence	Assess fidelity to the structured counselling format and content	Enhancing assessment of common therapeutic factors tool [40]; bespoke counselling evaluation form	Community health workers (CHWs)	During the last 2 months of the intervention
Qualitative assessments	Assess the acceptability, appropriateness, satisfaction, and feasibility of the selected HSS interventions	Topic guides for key informant interviews and focus group discussions	Pregnant and postnatal women involved in the intervention Healthcare workers involved in the intervention	During the last 3 months of the intervention

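### Before-after detection and referral rates taken from the bespoke registers and referral forms would be confounded with the introduction of those forms, and the Maternity Case Record review names no referral or abuse item to replace them

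*Protocol article*

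**What the plan says.** Two parts of the implementation phase bear on detection and referral rates.

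**Documentation reviews.** The text says that the rates "will be assessed before the intervention, and monitored weekly throughout the intervention period". It names two sources: "a review of the daily patient registers completed by ANC nurses" and "reviewing the referral forms completed by ANC nurses for patients who screen positive and agree to counselling". No other source is given for the earlier period. In Table 2 (Study designs) the tools for this review are "Bespoke patient registers and tracking forms", the timing is "Daily during the intervention period", and the objective is coverage.

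**Patient file reviews.** The text has fieldworkers extract the psychological distress questionnaire result from the MCR, both in the baseline period and throughout implementation. One stated purpose is to see whether detection and referral rates improved. The Table 2 objective is change in both rates for women with common mental disorders and for women experiencing domestic violence. Its timing cell reads "Weekly during the implementation phase" and mentions no baseline.

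**Origin of the tools.** The Development phase section says that the programme's tools were developed by the study. The nurse training module includes "completion of relevant stationery" (Addressing low levels of detection). On referral, the protocol says "Standardised referral pathways were developed" (Addressing poor linkage to care). The counselling by community health workers was also developed for the programme (Addressing the limited availability of treatment).

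**The concern.** A before-after comparison needs a source that records the same thing in the same way in both periods. The Documentation reviews text promises such a comparison from study-made forms for which Table 2 shows no baseline collection. The referral form raises a further difficulty: it is completed only when a woman agrees to counselling, and that counselling arrives with the programme. If recording starts or improves when the programme starts, recorded rates rise even if nurses' practice is unchanged.

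Low detection and poor linkage to care are two of the barriers that the programme targets, and the pilot's results are meant to shape a later cluster randomised trial. A gain that partly reflects new paperwork could mislead that design.

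**Working it through.** The protocol gives no rate, power or sample size for this comparison, so there is no figure to reproduce. The check sets the sections side by side.

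1. **Does the documentation review have a baseline?** Its text says yes; its Table 2 row gives only the intervention period. The two do not agree.

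2. **Could the registers supply one?** They are study-made. A baseline period does exist: two weeks, according to the Patient survey section. The protocol does not say whether registers run during it.

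3. **Could the referral forms supply one?** The form depends on agreement to counselling, and both the counselling and the standardised pathway are programme components. The Background reports that lack of standardised referral pathways was a barrier beforehand. The form has no evident earlier counterpart.

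4. **Does another source fill the gap?** The MCR is a routine record that contains the distress screen and has a place to record abuse (Background).

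| Outcome | Before-after source identified | Comparable in both periods? |
|---|---|---|
| Distress screening | MCR questionnaire result | Yes in the file-review text; Table 2 omits the baseline |
| Detection of domestic violence | Registers; no abuse item named in the file review | Not established |
| Referral | Registers and referral forms; no referral item named in the file review | Not established |

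5. **How would the artefact work?** Let d0 and d1 be the true rates before and during the intervention, and s0 and s1 the shares of events that the forms capture in each period. Then:

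   recorded ratio = (d1 × s1) / (d0 × s0) = (d1 / d0) × (s1 / s0)

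   The second factor is the recording artefact. With no true change (d1 = d0) and an assumed s1 of 0.8:
   - s0 = 0.8 gives 0.8 / 0.8 = 1.0, no artefact;
   - s0 = 0.4 gives 0.8 / 0.4 = 2.0, an apparent doubling;
   - s0 = 0 gives a recorded earlier rate of zero and an undefined ratio.

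   These values are assumptions that show the mechanism. The protocol gives neither s0 nor s1, so the result can lie anywhere from no artefact to a wholly artefactual change.

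**The case against.** The strongest reply is that the protocol already measures change from the MCR. Table 2 assigns change in rates to the file review and only coverage to the documentation review, and the file-review text includes the baseline period. This stands for distress screening. It does not stand for referral or domestic violence, because the only item the file review names is the distress questionnaire result.

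A second reply is that Table 2 dates data collection, not the existence of the forms. This also stands. A reader might infer that the forms exist only during the intervention, that the earlier rate is therefore zero by construction, and that the forms create the whole of any change. The documents support none of these as fact: study-made does not mean absent at baseline, and registers could have been placed in the baseline period. The stationery taught to nurses is not specified either, and could include the MCR itself.

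A reader might also argue that registers placed early would prompt screening and so spoil the baseline. That is possible but speculative, and it would shrink the apparent gain rather than inflate it.

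Nor does daily collection in Table 2 contradict weekly monitoring in the text: registers filled in daily and reviewed weekly is a natural reading.

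Finally, this is a three-facility pilot, and the article rests no sample size or progression rule on the register comparison. That limits the consequence but does not make the comparison sound.

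**Conclusion.** The point holds in a limited form. The text and Table 2 disagree on whether the documentation review has a baseline. A before-after change from its forms would be confounded with their introduction, most clearly for referral, where the form depends on a service that the programme brings in. The amount of artefact cannot be determined from the documents.

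Distress screening is largely protected by the MCR file review, provided that the baseline in its text is kept and Table 2 is corrected. For referral and for detection of domestic violence, no comparable before-after source is identified. The conclusion assumes that the sources named in the article are the ones to be used; a statement that registers ran before training would soften it for detection but not for the counselling-dependent referral form.

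**What to change.** - Take the before-after comparison from the MCR, with one extraction form used in both periods. Record the distress screen result, the abuse entry and any recorded referral.
- Use the bespoke registers and referral forms only for coverage and trends within the intervention period, in line with the Table 2 objective for that review.
- Remove the pre-intervention assessment from the Documentation reviews text. If registers do run before training, say so and report that baseline as not directly comparable.
- Correct the Table 2 timing for patient file reviews to include the baseline period.

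The cost is wording in two places and a few added fields in a review already planned. The downside is that before-after referral results are limited to what the MCR records. The documents do not say whether it records referral; if it does not, no before-after change in referral should be claimed.

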##### Counselling competence

The counselling competence of the CHWs delivering the counselling intervention will be measured during their first three counselling sessions. OTLs will be tasked with completing a counselling session evaluation form while observing the counselling sessions. The evaluation form will use a Likert scale and consist of questions assessing their verbal and non-verbal skills, as well as a checklist to evaluate the fidelity to the structured counselling format and content.

##### Qualitative assessments

Key informant interviews and focus group discussions with perinatal women, ANC nurses, CHWs, and OTLs will be used to assess the acceptability, appropriateness, satisfaction, and feasibility of the various HSS interventions.

#### Ethical approval and consent to participate

Ethical approval for the study has been obtained from the Human Research Ethics Committee at the University of Cape Town as well as from the Psychiatry, Nursing and Midwifery Research Ethics Subcommittee at King’s College London. In addition, the Western Cape Department of Health approved the use of the research sites. All participants will be asked to provide written, informed consent after the procedure is verbally explained to them. Participants will be informed of their right to withdraw from the study at any time without consequences. Pregnant women who are recruited into the cohort study will receive a ZAR100 food voucher after completing all questionnaires at recruitment and again at the 36-week follow-up interview.

#### Data handling and confidentiality

All data will be processed in accordance with the General Data Protection Regulation 2018 (GDPR). Participants will be allocated a unique identifier, which will be used to maintain confidentiality and minimise the use of personal information. Questionnaires completed in hard copy will be stored in a locked room at the University of Cape Town. King’s College London will be the data controller for the ASSET study.

#### Data analyses

A combination of mixed methods will be used to analyse the data collected. REDCap, a secure web platform for building and managing online databases and surveys, will be used to capture all quantitative data. Data will be exported to STATA/SE statistical software package version 15.1 (StataCorp., College Station, TX, USA) for analysis. Multiple imputation will be used to account for participants with incomplete data. Categorical variables will be described using frequency and percentages, and associations measured using chi-square tests. Continuous variables will be described using means and standard deviations, and associations measured using *t*-tests. Linear regression models will be used to evaluate for change in EPDS scores, adjusting for the clinic and any potential confounders. Implementation outcomes will be evaluated using multivariable regression models that adjust for relevant confounders and clinic.

Qualitative data will be analysed using NVivo 12 Pro qualitative data analysis software (QSR International Pty Ltd) [41]. Semi-structured interviews will be transcribed by bilingual speakers. Transcripts will be analysed using a thematic analysis approach to generate initial codes and define, search for, and review themes [42]. The development of initial codes will be guided to a certain degree by the interview topic guides. Further themes not captured by the initial coding will be identified through extensive reading of the transcripts and coding passages interpreted as important.

## Discussion

There is a substantial treatment gap for perinatal women with depression, anxiety, and exposure to domestic violence in low-resource African settings. We selected HSS interventions to improve awareness, detection, referral, and treatment of perinatal women experiencing symptoms of CMDs and domestic violence in Cape Town, South Africa. The purpose of this protocol is to describe how we will assess the effect of the HSS interventions on important implementation outcomes. The findings will help us refine the intervention components by identifying the barriers and facilitators experienced by the healthcare providers, their managers, and the patients receiving the intervention. While we aim to improve patient knowledge of domestic violence, and thereby improve their health-seeking behaviour, we do not intend to manage active cases of domestic violence by engaging with the perpetrators.

The findings will also inform us about the feasibility and acceptability of a variety of implementation and clinical outcome measures in this context. Lessons learnt from the pilot study will be incorporated into the design of a cRCT for which further funding will be sought. The integration of detection, referral, and care for perinatal women with depression, anxiety, and exposure to domestic violence into routine low-resource health facility and community settings is complex and requires a careful evaluation of process and outcomes, if it is to be scaled up for broader population benefit.

## Data Availability

The datasets used and/or analysed during the current study are available from the corresponding author on reasonable request.

## Abbreviations

AFFIRM: Africa Focus on Intervention Research for Mental Health
ANC: Antenatal care
BANC: Basic antenatal care
CBS: Community-based services
CHW: Community health worker
CMD: Common mental disorder
DoH: Department of Health
EPDS: Edinburgh Postnatal Depression Scale
EPOC: Effective Practice and Organisation of Care
HSS: Health systems strengthening
KTU: Knowledge Translation Unit
MOU: Midwife Obstetric Unit
MCR: Maternity case record
NPO: Not-for-profit organisation
OTL: Outreach team leader
PACK: Practical approach to care kit
TDF: Theoretical Domains Framework
ToC: Theory of change
WC: Western Cape
